### Recruitment {15}

The recruitment procedure will begin after approval has been obtained from the Institutional Review Board. Psychiatrists from specialist outpatient clinics in the Hospital Authority of Hong Kong, the largest public medical institution, will be asked to refer older adults with depression but without active suicidal ideation or recent suicide attempt (within the past month) who do not show an adequate response to current antidepressant treatment (i.e. residual depressive symptoms). The clinician investigators will assess the potential subjects according to the exclusion and inclusion criteria as stated below. The diagnosis will be confirmed using the Structured Clinical Interview for Diagnostic and Statistical Manual Mental Disorders. Medical health history and treatment will be assessed by direct patient inquiry and confirmed using the patients’ electronic health records provided by the Hospital Authority. The subjects will be informed that the HD-tDCS treatment study will involve an off-label treatment, and the possible risks and side effects will be clearly explained.

## Assignment of interventions: allocation

### Sequence generation {16a}

Block randomization will be used in this study. Each block will consist of eight participants at a 1:1 ratio between the two groups. In the randomization procedure, each participant will be assigned a special number generated by a computer. These numbers will not be decoded until the intervention group is assigned.

### Concealment mechanism {16b}

An independent team member, who will not be involved in the enrolment, intervention, or assessments, will perform the randomization process. The participants and investigators responsible for assessment and data analysis will be blinded to the group allocation.

### Implementation {16c}

If participants are interested in participating in the treatment, psychiatrists will explain the study information and recruit them after screening out for exclusion criteria by collecting their contact information. Then, participants are contacted by telephone by the investigator. The investigator will inform the participants about the study and verify that the participants are aware of the implications of participation in a trial and propose an appointment for the initial evaluation. The participants will be given at least a month to consider whether or not to join the study. After the approval to join the study, participants are randomized to either the active HD-tDCS group or the sham HD-tDCS group by the research coordinator for subsequent intervention. Participants will then be contacted with the schedule and details of the treatment.

## Assignment of interventions: Blinding

### Who will be blinded {17a}

Trial participants and the trained investigator performing the interventions are double-blinded.

### Procedure for unblinding if needed {17b}

N/A. If there was a situation such as a medical need or emergency which required unblinding, the principal investigator will be informed and make the final decision.

## Data collection and management

### Plans for assessment and collection of outcomes {18a}

A trained clinician investigator who is not involved in the intervention or randomization procedure will perform the assessments. The primary and secondary outcomes will be assessed at baseline, immediately after the intervention, and 4 and 12 weeks after the intervention.

### Plans to promote participant retention and complete follow-up {18b}

To reduce the drop-out rate, each of the participants’ case medical officers will be alerted to remind the participants to attend all interventions and assessments. In addition, the benefits and side effects of HD-tDCS will be clearly explained during enrolment, and materials related to this study will be provided to both the participants and their caregivers. The participants and their caregivers will receive two reminder telephone calls (1 week and 1 day) before interventions and assessments. If a participant fails to attend an appointment, they will be called to rearrange the appointment. A direct hotline within office hours will be provided to the participants and their caregivers in case of any concerns or problems.

### Data management {19}

For each participant, clinical information regarding the diagnosis, description of clinical condition, severity of depression and the modalities of treatment and management are stored in the Clinical Management System (CMS) managed by the Hospital Authority (HA). Subsequently, formally trained research assistants will be responsible for collecting patient information and report in a data record form, first in a paper format and then electronically. The paper format data will be locked in a cabin in the office and electronic data is encrypted with passwords only available by the research assistants and data manager. The data manager will perform additional computerized consistency tests to detect the presence of non-standard, missing, aberrant or incoherent data. These tests will be executed regularly during the participants’ recruitment and monitoring. Each identified incoherence will be the subject of a request for clarification to the researcher. The data will be destroyed after 5 years commencing from the completion of the study.

### Confidentiality {27}

Personal information of participants will be collected at the initial interview, an identifier will be assigned to each enrolled participant. Information of participants will be encoded in an encrypted file with a password only available by the research assistants and data manager.

### Plans for collection, laboratory evaluation and storage of biological specimens for genetic or molecular analysis in this trial/future use {33}

N/A. No biological specimens will be collected in this study.

## Statistical methods

### Statistical methods for primary and secondary outcomes {20a}

The primary outcome measurement is HAMD-17. The effect power of intervention is measured by the change of HAMD-17. If the results showed a significant improvement in the HAMD-17 measurement, it represents the intervention is effective. Both clinical response rate and remission rate are also depending on the measurement of HADM-17. They are used as an indication for the real clinical impact of the intervention. A clinical response will be defined as a reduction of 50% or more in the HAM-D-17 score. A HAMD-17 score of 7 or less will be used as an indicator of remission. Therefore, a significant result in the area of either clinical response or remission rate will indicate the clinical impact of the intervention.

To examine the presence of any group differences in demographics and clinical profile between the treatment and the sham groups at baseline, chi-squared tests and *t*-tests will be performed for categorical and continuous variables respectively.

Two-way repeated measures analysis of variance (ANOVA) will be used to examine the effect of time and treatment conditions on the HAM-D-17 scores and other cognitive and IADL measurements across various assessment time points. The analysis would be adjusted to age, sex, medication type/dose, relapse episodes and other potential confounders. If both depressive symptoms and cognitive function improved, mediation analysis will be done to determine the cognitive function improvement is mediated by the improvement of depressive symptoms or vice versa.

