### Trial design {8}

The study described in this protocol is a RCT to evaluate the superiority of an active HD-tDCS programme for patients with LLD compared with the sham HD-tDCS programme. Forty-eight patients with LDD will be randomized (1:1) in the active HD-tDCS group or the sham HD-tDCS group.

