### Methods for additional analyses (e.g. subgroup analyses) {20b}

Post hoc analyses will also be performed with Bonferroni corrected t-tests to investigate the improvements in all outcome variables in pairwise comparisons across various assessment time points. Statistical significance will be set at a *p* value < 0.05. Intention-to-treat last-observation carried-forward scores will be used for the analyses. All computations will be performed using SPSS for Windows, version 22.0.

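### The stated success rule calls the intervention effective on a significant HAMD-17 improvement without requiring a difference from sham

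*Protocol article*

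**What the plan says.** The trial design section (8) gives the aim: "to evaluate the superiority of an active HD-tDCS programme for patients with LLD compared with the sham HD-tDCS programme". The sample size section (14) likewise sizes the trial for a difference between groups.

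The statistical methods section (20a) then says how the result will be judged. On the measure: "The effect power of intervention is measured by the change of HAMD-17". On the conclusion: "If the results showed a significant improvement in the HAMD-17 measurement, it represents the intervention is effective". On the binary outcomes: "a significant result in the area of either clinical response or remission rate will indicate the clinical impact of the intervention". None of these three sentences mentions sham.

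The model follows: "Two-way repeated measures analysis of variance (ANOVA) will be used to examine the effect of time and treatment conditions on the HAM-D-17 scores". Neither the treatment-by-time interaction nor a between-arm difference in change is named as the test that supports the efficacy claim.

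The section on additional analyses (20b) adds post hoc, Bonferroni-corrected t-tests "to investigate the improvements in all outcome variables in pairwise comparisons across various assessment time points". Assessments take place "at baseline, immediately after the intervention, and 4 and 12 weeks after the intervention" (18a). The primary outcome section places the primary outcome at 12 weeks after the intervention.

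**The concern.** A superiority trial against sham needs a success rule that refers to sham. In a two-arm repeated measures ANOVA, three different results could be described as a significant improvement: a time effect pooled over both arms, a before-after change in the active arm, or a greater change in the active arm than in the sham arm. Only the third answers the trial's question, and the text does not single it out.

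Improvement in both arms is foreseeable. Patients enter on a HAMD-17 threshold (8 or more), so some regression to the mean is likely, and a sham response is likely too. Remission is a score of 7 or less, so a patient who enters at 8 remits with a one-point fall. If shared improvement counts as efficacy, the sham arm no longer protects the primary conclusion, and a reader of the published protocol could not say that the prespecified rule had been broken.

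**Working it through.** **1. The plan's own figure.** The protocol gives a standardised difference of 0.743, 80% power, alpha 5% and 24 per arm. For a two-sample t-test the noncentrality is 0.743 × √(24/2) = 2.574. One-sided, 24 per arm gives 81.3% power, which reproduces 48. Two-sided, 24 per arm gives 71.2% and 30 per arm would be needed. The protocol does not state sidedness. What matters here is that the calculation is for a between-arm test, so the design and the success rule do not speak of the same contrast.

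**2. Inputs for the error rates.** From the protocol: 24 per arm, and four assessments, hence 4 × 3 / 2 = 6 pairs of time points. Assumed, because the protocol gives no figure: no treatment effect; equal variance at each visit; correlation 0.5 between visits; and the same improvement *d* in both arms, present at all three later visits, with *d* = 0.3, 0.5 or 0.8 SD.

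**3. ANOVA time effect.** The visit means are (0, −*d*, −*d*, −*d*), whose squared deviations sum to 0.75*d*². The F noncentrality is 48 × 0.75*d*² / (1 − 0.5) = 72*d*², on 3 and 138 degrees of freedom, with a 5% critical value of 2.67.

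**4. Active-arm t-test, baseline to week 12.** The SD of the change is √(2 × (1 − 0.5)) = 1 SD, so the noncentrality is *d* × √24, on 23 degrees of freedom. With Bonferroni for six pairs, alpha is 0.05/6 and the two-sided critical value is 2.886. Only significance in the direction of improvement is counted.

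| Shared improvement *d* | 0.3 SD | 0.5 SD | 0.8 SD |
|---|---|---|---|
| F noncentrality, 72*d*² | 6.48 | 18.0 | 46.1 |
| Time effect significant | 54% | 95% | 100% |
| t noncentrality, *d*√24 | 1.47 | 2.45 | 3.92 |
| Active arm significant, uncorrected | 29% | 65% | 96% |
| Active arm significant, Bonferroni | 10% | 35% | 84% |

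**5. Check by simulation.** With 2,500 simulated trials per setting, the time effect was significant in 54%, 96% and 100%, and the Bonferroni-corrected active-arm test in 10%, 35% and 84%. At 29 per arm the corresponding figures were 64%, 98% and 100%, and 14%, 47% and 92%.

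**6. Between-arm tests on the same simulated data.** The treatment-by-time interaction and the t-test on the difference in week-12 change were significant in 4.1% to 5.5% of trials, whatever the shared improvement. Bonferroni lowers the rate for the active-arm test but does not hold it at 5%, because it corrects the number of tests and leaves the contrast unchanged.

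**The case against.** The best defence is that the document supplies the comparator elsewhere. The aim is superiority over sham, the sample size is for group differences, the discussion describes a comparison of active with sham stimulation, and the ANOVA includes treatment, so the right test is available. In that context the sentence may simply be loose wording for active against sham. This stands as evidence of intent. It does not repair the rule, because the one place that says what counts as effective leaves the comparator out.

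A second defence is that the deciding contrast can be left to a fuller protocol or an analysis plan. That would answer an omission. Here the article does state a rule for success, and later detail would have to correct that rule and not just add to it.

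Two stronger readings are tempting and should be resisted. A reader might infer that the protocol declares efficacy on the time-point t-tests. It does not: section 20b calls them post hoc and draws no conclusion about effectiveness from them, and its wording could even cover arm contrasts at each visit. A reader might also infer that the plan would give a false efficacy claim most of the time. That depends on which test is taken to decide and on an improvement that the documents do not give. It fits the time effect over the range shown, but the protocol never names that effect as the efficacy test. The corrected active-arm test passes one half only at 0.8 SD among the sizes shown.

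**Conclusion.** Wrong as written. The rule for effectiveness and the parallel rule for response and remission do not require a difference from sham, and the ANOVA sentence leaves the deciding effect open. Improvement shared with sham can therefore satisfy a rule in a trial whose aim is superiority over sham. The between-arm intent is clear, so this is a fault in the stated rule. It is not evidence that a before-after analysis is planned.

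The size depends on the reading: 54% to 100% if the time effect decides, 10% to 84% if the corrected active-arm test decides, and about 5% if a between-arm test decides. These figures rest on the assumed correlation of 0.5 and the assumed shared improvement of 0.3 to 0.8 SD. The fault in the wording does not depend on either assumption.

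**What to change.** Replace the effectiveness sentence in section 20a with: *Efficacy is concluded only if the between-arm difference (active minus sham) in HAMD-17 change from baseline to 12 weeks after the intervention, from the primary model, is significant at two-sided p < 0.05.*

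State beside it that response and remission are compared between arms at the same time point. In section 20b, label the time-point t-tests as descriptive and add between-arm contrasts at each visit. The within-arm comparisons can stay, since they describe the course over follow-up.

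The cost is a few sentences and no new data, and the change should be made before unblinding. Stating a two-sided test also makes visible that 24 per arm gives 71.2% power for the assumed 0.743, and 29 per arm 79.4%. That is a separate matter for the sample size section and no reason to leave the rule as it is.

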**Methods:**

Fifty-eight patients with LLD will be recruited and randomly assigned to the active HD-tDCS or sham HD-tDCS group. In both groups, patients will receive the active or sham intervention in addition to their pre-existing antidepressant therapy, for 2 weeks with 5 sessions per week, each lasting 30 min. The primary outcome measures will be the change of depressive symptoms, clinical response and the remission rate as measured with the Hamilton Depression Rating scale (HAMD-17) before and after the intervention, and at the 4th and 12th week after the completed intervention. Secondary outcome measures include cognitive symptoms, anxiety symptoms, daily functioning and adverse effects.

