##### Primary outcome

The primary outcome will be the change of depressive symptoms, the clinical response rate and the remission rate as measured with the HAMD-17 at 12 weeks after the completed intervention. HAMD-17 is a widely used and reliable measure of depressive symptoms [21]. Scores range from 0 to 52, with higher scores indicating more severe depression. A clinical response will be defined as a reduction of 50% or more in the HAM-D-17 score in old age adult patients. A HAMD-17 score of 7 or less will be used as an indicator of remission [20].

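### Three unranked primary outcomes, and a significant result on either binary one may support a clinical-impact claim, with no error control across them

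*Protocol article*

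**What the plan says.** The Primary outcome section states: "The primary outcome will be the change of depressive symptoms, the clinical response rate and the remission rate as measured with the HAMD-17", assessed 12 weeks after the end of the intervention. The abstract's Methods paragraph lists the same three: "The primary outcome measures will be the change of depressive symptoms, clinical response and the remission rate as measured with the Hamilton Depression Rating scale". Neither place ranks them.

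The section on statistical methods for primary and secondary outcomes {20a} attaches a conclusion to each route. For the continuous score: "If the results showed a significant improvement in the HAMD-17 measurement, it represents the intervention is effective". For the two rates: "a significant result in the area of either clinical response or remission rate will indicate the clinical impact of the intervention". The second statement is not made conditional on the first.

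The section on additional analyses {20b} gives the only threshold, "Statistical significance will be set at a *p* value < 0.05", and the only multiplicity adjustment, "Bonferroni corrected t-tests to investigate the improvements in all outcome variables in pairwise comparisons across various assessment time points".

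The Sample size section {14} rests on one comparison of continuous depression severity: Hedges' g = 0.743, 80% power, alpha 5%, 48 evaluable patients (24 per group), 58 recruited (29 per arm).

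**The concern.** Two outcomes labelled primary are joined by an OR rule, and each may reach significance at the full 5%. With no treatment effect, two chances at 5% give a false claim more often than one chance does. The Bonferroni correction does not help: it addresses pairs of visits, it is written for t-tests, and the two rates are proportions.

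The trial could also miss on HAMD-17 change, the kind of outcome it was sized for, and still report clinical impact on a primary outcome because one dichotomy of the same scale crossed 0.05. At 24 to 29 patients per arm, a few patients on one side of a cut-off can decide that.

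**Working it through.** **1. The plan's own figure.** For a two-sample t-test (noncentral t) with g = 0.743 and 80% power, one-sided 5% needs 24 per group, so 48. Two-sided 5% needs 30 per group, so 60. The stated 48 therefore reproduces as a single one-sided test of one continuous outcome. The undeclared sidedness is a separate matter. What counts here is that the calculation leaves no room for a second or third primary test.

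**2. Ceiling if the tests were independent.**
- Either of two: 1 − 0.95² = 0.0975, or 9.75%.
- Any of three: 1 − 0.95³ = 0.1426, or 14.3%.

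All three outcomes come from one scale, so the tests are positively correlated and these are approximate upper limits. With normal test statistics all correlated at 0.9, the figures are still 7.0% and 8.4%.

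**3. Null simulation using the plan's definitions.** From the article: entry score of 8 or more, response as a reduction of at least 50%, remission as a score of 7 or less, and 24 or 29 per arm. Assumed, because the article gives no values: baseline mean 14-20 (SD 4), follow-up mean 9-12 (SD 5), and baseline-to-follow-up correlation 0.3-0.7. Also assumed: a two-sided t-test on change, standing in for the planned ANOVA, and uncorrected chi-squared tests on the rates. Each setting had 20,000 trials. Results at correlation 0.5:

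| Per arm | Baseline / follow-up mean | Either rate p < 0.05 | Any of three p < 0.05 | Any of three, Bonferroni over three |
|---|---|---|---|---|
| 24 | 14 / 9 | 8.4% | 11.3% | 3.9% |
| 24 | 16 / 10 | 8.5% | 11.8% | 4.3% |
| 24 | 20 / 12 | 9.3% | 12.1% | 4.0% |
| 29 | 14 / 9 | 7.5% | 10.6% | 4.0% |
| 29 | 16 / 10 | 7.6% | 10.7% | 4.0% |
| 29 | 20 / 12 | 8.4% | 11.4% | 4.0% |

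Correlations of 0.3 and 0.7 change little. Over all settings the ranges are about 7-9% for either rate and about 10-12% for any of the three.

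**4. Dependence on the test.** With Fisher's exact test for the rates, the same kind of simulation gives about 4-5% for either rate and about 8% for any of the three.

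**5. Impact claimed without effectiveness.** With chi-squared tests, 5-7% of null trials have a significant response or remission result while HAMD-17 change is not significant. The either-or rule would claim clinical impact in all of these.

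**6. Cost of splitting alpha instead.** Bonferroni over three sets each test at 0.05/3 = 0.0167. At g = 0.743 and 24 per group, power for HAMD-17 change falls from 71% to 54% two-sided, or from 81% to 65% one-sided. Restoring 80% needs 40 per group (80 evaluable) two-sided, or 34 per group (68 evaluable) one-sided. A hierarchy that starts with HAMD-17 change needs no extra patients for multiplicity.

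**The case against.** The strongest reply is that the article does not treat the three outcomes alike. Section {20a} calls HAMD-17 the primary outcome measurement, bases the effectiveness conclusion on its change alone, and presents the two rates as indicators of clinical relevance. This stands in part. A reader might infer that a win on any of the three makes the trial positive, but the article does not say so, and the 10-12% figure applies only on that reading. It does not remove the either-or rule, which concerns two outcomes labelled primary and is not gated on HAMD-17.

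A reader might also take the abstract's list of visits as making every outcome primary at every visit, giving nine unadjusted tests and a far larger error rate. The documents do not support this. The Primary outcome section fixes 12 weeks, {20a} analyses HAMD-17 across visits in one repeated-measures ANOVA, and the pairwise visit comparisons carry Bonferroni.

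The test for the rates is unnamed; chi-squared is mentioned only for baseline comparisons. This objection stands, which is why both test results are shown. Fisher's exact test brings the either-or rule to about 5% or just under, but only because it is conservative in small samples. That is not a planned control and does not gate the claim on HAMD-17.

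Finally, a separate analysis plan may deal with multiplicity. The point does not rest on silence, however: the protocol states three primaries, an either-or rule and one threshold. A plan that imposed a hierarchy would contradict that wording, so the wording has to change anyway.

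**Conclusion.** The concern holds in a limited form. Error is uncontrolled across the three primary outcomes, and the stated either-or rule lets a clinical-impact claim stand without a significant HAMD-17 change. With no treatment effect, that rule gives a false claim in about 7-9% of trials with chi-squared tests, or about 4-5% with Fisher's exact test. If a win on any of the three counted as success, the figures would be about 10-12% and about 8%.

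These figures rest on assumed HAMD-17 means, SDs and correlations, on 24 to 29 per arm, and on a t-test for change. It would be too strong to say that the plan has no multiplicity control at all, since comparisons between time points are corrected. It would also be too strong to say that the effectiveness claim itself is inflated: that claim rests on HAMD-17 change alone.

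**What to change.** - Name HAMD-17 change at 12 weeks after the intervention as the sole primary outcome, and align the abstract with this. The 12-week point comes from the Primary outcome section. The sample size supports the choice of a continuous severity measure but gives no time point.
- Make response and remission key secondary outcomes, tested only if the primary is significant, either in a prespecified order (for example response, then remission) or with Holm across the two.
- Delete the either-or sentence, and name the test to be used for the two rates.

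With this gate, a false clinical-impact claim under no effect also requires a false positive on the primary, so the chance of any false claim across the three stays at or below 5%.

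The cost is protocol wording, to be settled before unblinding. No patients are added. The downside is that response or remission alone can no longer support a primary claim.

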### Eligibility criteria {10}

The inclusion criteria are as follows:Sixty years of age or aboveRight-handedness, as determined by the Edinburgh Handedness Inventory (to homogenize neuroanatomical targeting)Chinese ethnicityFulfil the criteria of major depressive disorder (single or recurrent episode) and in partial remission, defined by the 5th Edition of the Diagnostic and Statistical Manual of Mental Disorders (DSM-5)Presence of mild to severe levels of depressive symptoms measured and defined by HAMD-17 scores ≥ 8 and ≤ 52 [20]Suboptimal treatment response with at least one adequate antidepressant trial defined as full or best tolerated doses at least 6 weeksStable dosage of antidepressants or other treatments for depression in recent 4 weeksValid informed written consent

The exclusion criteria are as follows:A DSM-5 diagnosis other than depressive disorders (e.g. bipolar and related disorders, schizophrenia spectrum and other psychotic disorders).A Hong Kong Chinese version of the Montreal Cognitive Assessment (HK-MoCA) score below the second percentile according to the subject’s age and education level (to exclude subjects with existing dementia)Substance use disorderActive suicidal ideation or a suicide attempt within the past monthConcomitant unstable medical conditions or major neurological conditionsSignificant communication impairment

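### HAMD-17 is analysed as change from baseline with an open-ended covariate list that does not name baseline HAMD-17: valid, but less precise than it need be, and not fixed in advance

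*Protocol article*

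**What the plan says.** All of this stands in the protocol article.

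- **Model** (Statistical methods for primary and secondary outcomes): "Two-way repeated measures analysis of variance (ANOVA) will be used to examine the effect of time and treatment conditions on the HAM-D-17 scores".
- **Covariates** (same section): "The analysis would be adjusted to age, sex, medication type/dose, relapse episodes and other potential confounders". Baseline HAMD-17 is not named here or anywhere else as a covariate, and no rule says what may enter under the closing clause.
- **Effect measure** (same section): "The effect power of intervention is measured by the change of HAMD-17".
- **Visits** (Plans for assessment and collection of outcomes): the outcomes are "assessed at baseline, immediately after the intervention, and 4 and 12 weeks after the intervention", so baseline is one of four time points. The Primary outcome section takes the result "as measured with the HAMD-17 at 12 weeks after the completed intervention".
- **Baseline tests** (Statistical methods, just before the model): chi-squared tests and t-tests are planned, with the purpose "To examine the presence of any group differences in demographics and clinical profile between the treatment and the sham groups at baseline".
- **Blinding** (Concealment mechanism): the investigators who analyse the data are to be blind to allocation.

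**The concern.** Two features of one short paragraph matter here.

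The first is precision. If baseline is a level of the time factor, the treatment effect is read from the time-by-group term, which compares change from baseline between arms. Subtracting the whole baseline score is efficient only when baseline and follow-up are almost perfectly correlated. Using baseline as a covariate lets the data set the weight. In a trial of this size the difference can matter, and baseline HAMD-17 is already collected.

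The second is that the covariate list never closes. The Discussion names further possible confounders: antidepressant type, degree of suboptimal response and resistance, and symptom duration. The baseline tests stand directly before the adjustment sentence. Under randomisation any baseline difference is due to chance, so those tests are no guide to what should be adjusted for. With an open list, the reported result can depend on a choice of covariates made after the data are in.

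**Working it through.** **1. The plan's own figure.** Inputs from Sample size: Hedges' g = 0.743, alpha 5%, power 80%, 24 per group. Sidedness is not stated. A two-sample t-test (noncentral t) gives:

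- one-sided 5%: 24 per arm needed, with power 81.3% at 24, which reproduces the stated number;
- two-sided 5%: 30 per arm needed, with power 71.2% at 24 and 79.4% at 29 (the recruitment target per arm).

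The illustration below uses two-sided 5% and 24 per arm. Both are my choices for the comparison.

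**2. Variance of the two contrasts.** Assume the same SD at baseline and week 12, with correlation ρ. Relative to the variance of a final score:

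- change from baseline: 2(1 − ρ);
- adjusted for baseline: 1 − ρ²;
- ratio, adjusted to change: (1 − ρ²) / [2(1 − ρ)] = (1 + ρ)/2.

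The protocol does not give ρ, so a range is assumed.

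| ρ (assumed) | Change, 2(1 − ρ) | Adjusted, 1 − ρ² | Ratio | Variance cut |
|---|---|---|---|---|
| 0.3 | 1.40 | 0.91 | 0.65 | 35% |
| 0.5 | 1.00 | 0.75 | 0.75 | 25% |
| 0.7 | 0.60 | 0.51 | 0.85 | 15% |

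**3. Power as a single-contrast illustration.** Noncentrality is d√(n/2) = d√12 at n = 24 per arm, with 46 degrees of freedom for change and 45 with baseline as a covariate.

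*If 0.743 is on the change-score SD*, change-score power is 71% throughout. Adjustment raises d to 0.743/√[(1 + ρ)/2]:

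| ρ | d after adjustment | Power, change | Power, adjusted |
|---|---|---|---|
| 0.3 | 0.743/√0.65 = 0.92 | 71% | 88% |
| 0.5 | 0.743/√0.75 = 0.86 | 71% | 83% |
| 0.7 | 0.743/√0.85 = 0.81 | 71% | 78% |

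*If 0.743 is on the final-score SD*, both contrasts depend on ρ:

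| ρ | d, change | d, adjusted | Power, change | Power, adjusted |
|---|---|---|---|---|
| 0.3 | 0.743/√1.40 = 0.63 | 0.743/√0.91 = 0.78 | 57% | 75% |
| 0.5 | 0.743/√1.00 = 0.74 | 0.743/√0.75 = 0.86 | 71% | 83% |
| 0.7 | 0.743/√0.60 = 0.96 | 0.743/√0.51 = 1.04 | 90% | 94% |

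On either scale the gain shrinks as ρ rises: 17, 12 and 7 points on the first, and 18, 12 and 4 on the second.

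**4. The open list.** A simulation (3,000 runs per scenario, 24 per arm, no true effect) reported the most favourable subset of optional covariates, each assumed to explain 0% or 5% of the variance. Two-sided type I error was 6.6% and 8.2% with three optional covariates, and 9.2% and 14.1% with five. A model with all covariates fixed gave 4.6% to 5.7%. This is a deliberate worst case on assumed covariates. It shows why the list should be closed and does not forecast this trial's error rate.

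**The case against.** The strongest reply is that baseline is already used. The time-by-group contrast on change is unbiased under randomisation, so the choice between change and covariate adjustment is one of efficiency and not an error. That stands, and the point is put no higher. The size also rests on a correlation that the document does not give, and a single t-type contrast is not the power of a four-visit ANOVA with covariates. Both limits stand too. A covariate list may also be completed in an analysis plan that is not shown; but this protocol does state a list, omits baseline severity from it and leaves its end open.

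Several stronger readings are tempting, and the document does not support them:

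- *Covariates will be picked by p-value.* The text gives the baseline tests no such role. Analysts are blinded and, under Interim analyses, statistical analysis waits until the trial is over. This lessens the risk of data-driven choice but does not remove it, because nothing fixes the list.
- *The trial is already short of 80% power.* That holds for a two-sided test at 24 per arm (71.2%). One-sided it is 81.3%, and two-sided at 29 per arm it is 79.4%. It is a sample-size question and is not needed here.
- *Adjustment gains most when the correlation is high.* This follows only if adjusted power on the final-score SD (75% / 83% / 94%) is set against the 71% of an unadjusted final-score comparison. The plan's contrast is change, with 57% / 71% / 90%.
- *Remission, response and the secondary scales go unadjusted.* Entry at "HAMD-17 scores ≥ 8 and ≤ 52" with remission at 7 or less does tie remission to baseline, since a patient at 8 needs a fall of one point. But the article states no model for response or remission, and models of that kind, like baseline terms for the secondary scales, can be left to the analysis plan.
- *Post-randomisation dose will be adjusted for.* Medication and dose are recorded at baseline, and the existing regimen is to be continued until the post-intervention assessments are complete. The covariate merely carries no date.

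**Conclusion.** The point holds as one of efficiency and pre-specification. On its most natural reading, the primary HAMD-17 analysis is a valid change-from-baseline contrast that gives up precision by not adjusting for baseline HAMD-17, and its covariate list is not closed. The variance given up is 35% / 25% / 15% of the change contrast at ρ = 0.3 / 0.5 / 0.7, worth roughly 4 to 18 points of power in the illustration, depending on ρ and on the scale of the planning effect. This assumes equal SDs at the two visits, baseline as a level of time, and the week-12 contrast as the quantity of interest. The variance ratio is exact under those assumptions; the power figures are illustrative. The document shows neither bias in the planned contrast nor an intention to choose covariates by their p-values.

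**What to change.** Fit the HAMD-17 model to the three post-baseline visits (immediately after the intervention, then 4 and 12 weeks later), with baseline HAMD-17 as a covariate. Add a short closed list of baseline covariates, for example age, sex and number of prior episodes, with any medication covariate taken at baseline. Fix the list in writing before unblinding. Move the closing clause on further confounders to a labelled sensitivity analysis, and replace the baseline significance tests with descriptive summaries by arm. If an analysis plan already does this, the protocol needs only to refer to it.

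The cost is wording only: baseline HAMD-17 is already collected, and no visit, measurement or patient is added.
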